### Eligible participants

The outpatient or inpatient cases of cardiology department of Zhongda Hospital and Jinling Hospital were selected. Patients to be enrolled must meet all inclusion criteria listed in Table 1 and not meet any of the exclusion criteria. The inclusion criteria and exclusion criteria are listed in Table 1. A list of patients who recently underwent echocardiography and polysomnography at the department of cardiology and signed a form consenting to participate in research will be generated. Those patients with an apnea–hypopnea index greater than 15 events/hour and left ventricular ejection fraction less than 40 will be selected and contacted by telephone. The acceptors will be asked to visit the research center where the informed consent process will be conducted.

**Table 1 Tab1:** Inclusion and exclusion criteria

Inclusion criteria	Exclusion criteria
1) Voluntarily participate, understand and sign the informed consent;	1) Have participated in other clinical studies
2) Symptomatic chronic heart failure, NYHA grade II–IV, chronic heart failure diagnosis according to ESC Guidelines for Heart Failure 2016 and China Guidelines for Heart Failure 2018; the condition is relatively stable, without intravenous medication	2) Hemodynamic instability
3) LVEF 40% or less	3) Allergic to drugs or their ingredients
4) Over 18 years old, less than 80 years old	4) Acute myocardial infarction
5) The patient has received standard optimized treatment for HFrEF and is treated according to the recommended drug dose in the guidelines, unless contraindication or intolerance	5) Active liver disease or severe liver insufficiency
6) eGFR ≥ 45 ml/min/1.73 m^2^	6) Known active infection or severe blood disease or endocrine dysfunction
7) Diagnosis of OSAHS according to the Diagnostic Guidelines for Adult Obstructive sleep apnea (2016); AHI ≥ 15 events/h	7) History of COPD, asthma, or other serious lung diseases
	8) History of stroke, peripheral or central nerve abnormalities, cerebrovascular disease
	9) Pregnant and lactating women
	10) HbA1c ≥ 7.0%
	11) Previous use of dapagliflozin

Screening for GFR estimates < 30 mL/min/1.73 m^2^ as measured by a simplified MDRD formula using serum creatinine level, age, sex, and race [24]

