## Methods/design

### Study design

This study is a prospective, multicenter, randomized controlled superiority trial. The study will be conducted in two research centers (Zhongda Hospital and Jinling Hospital). This paper presents the design and protocol for the trial according to the Standard Protocol Items: Recommendations for Interventional Trials (SPIRIT) statement [22].

An overview of the study design and timeline for participants is provided in Fig. 1. Those eligible for dapagliflozin treatment and treated in real-life conditions will be invited to participate. Following the inclusion and exclusion criteria, a pre-therapeutic evaluation will be conducted [physical examination, echocardiography, laboratory testing, Minnesota Living with Heart Failure Questionnaire and EuroQol Group 5-Dimension Self-Report Questionnaire (EQ-5D), Epworth Sleepiness Scale, nocturnal ventilatory polygraphy] [20].

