**Fig. 1 Fig1:**
[figure not shown]
Study design overview

Patients will be divided into two groups:Group 1: patients received optimized heart failure therapy plus dagaglizin 10 mg daily, dapagliflozin will be started the day after the polygraphyGroup 2 (control group): patients received only optimized heart failure therapy

“Optimal drug therapy” in large heart failure trials usually refers to a combination of BBL, ACE inhibitors or ARBs and MR antagonists, with an optimal dose [23]. After 3 months of treatment, the final evaluation will include physical examination, echocardiography, laboratory testing, Minnesota Living with Heart Failure Questionnaire and EQ-5D, Epworth Sleepiness Scale, and nocturnal ventilatory polygraphy for all patients included in the study. During the research process, the participants cannot take other types of SGLT2 inhibitors such as empagliflozin and canagliflozin. Using ventilators to treat sleep apnea is not allowed; if it is necessary, they will withdraw from the study.

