### Follow-up and duration of the study

There will be two visits at the clinical research center, one before (baseline) and one after (3 months follow-up) the dapagliflozin intervention. Data collection to assess efficacy of the intervention will be managed by research team members. An overview of the measures used at each of the four time points is illustrated in Table 2. For improving the compliableness of patients, the strategies are as follows: (1) adhere to the principle of voluntary participation and explain the benefits of this study to the participants and the importance of treatment and adherence to the treatment. Health education process could increase the related knowledge, change the behavior, and enhance the compliance of patient. (2) Written informed consent will be obtained from each patient before they begin the trial. All participants will fill in informed consents. (3) The treatment is free for participants, such as the relevant examination expenses and the telephone bill, traffic expenditures, and analgesic drugs incurred during the treatment and follow-up. (4) Record participants’ contact methods in detail, including mobile phone, WeChat, and e-mail for contact and follow-up.

**Table 2 Tab2:** Administration of study measures by assessment period

Research phase	Screening and randomization	Treatment period		
Interview	1	2	3	4
Research date	− 7–0	28 ± 2	56 ± 4	84 ± 6
Baseline information				
Informed consent	●			
General information	●			
History	●			
Physical examination	●	●	●	●
Treatment				
Inclusion/exclusion criteria	●			
Combined medication	●	●	●	●
Compliance		●	●	●
Completion of research				●
Inclusion/exclusion criteria				
PSG	●			
Echocardiography	●			
Security index				
Blood routine	●			●
Urine routine	●			●
Blood biochemical	●			●
Electrocardiogram	●			●
Adverse event assessment		●	●	●
Outcome				
AHI	●			●
Epworth Somnolence Scale (ESS)	●	●	●	●
Echocardiography	●			●
NT-proBNP	●			●
Quality of life as measured by the Minnesota Living with Heart Failure Questionnaire	●	●	●	●
EQ—5D—3L				
L_SpO2_	●			●
Inflammatory factors	●			●

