### Sample size

The sample size calculation for this trial was performed using the PASS 11.0 program [25]. The primary end point of the main study was the decreasing value of Apnoea–Hypopnoea Index (△AHI). Based on existing data, a 8 ± 6 events/h change in AHI events/h between the control and therapy groups was considered clinically relevant (assuming that AHI would not change in the control group) [26–28]. Based on a power of 90% and an alpha value of 5%, it was calculated that a sample size of 30 patients (considering the 20% sample loss rate) would be sufficient to detect a difference in the effect size of at least 10%. Data monitors from the two centers will supervise the study process at a fixed period.

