## Discussion

As a result of untreated OSA, hypertension, cardiovascular disease, metabolic disorders, and neuropsychiatric problems can be significantly worsened [29]. As a result of periodic airway collapses, OSA causes sleep fragmentation and intermittent hypoxia. These phenomena lead to an increase in oxidative stress, reactive oxygen species formation, increased inflammation via the NF-kB pathway [30], sympathetic activation [31], metabolic dysregulation, and endothelial dysfunction [32] resulting in insulin resistance [33], hypertension, and cardiovascular diseases.

In patients with symptomatic OSA, positive airway pressure (PAP) is the primary treatment option. Treatment of OSA with PAP has some limitations. Patient adherence is reported to be poor with an averagemask use of 4.4 h/night [34]. Additionally, CPAP therapy has a limited effect on blood sugar control. There are currently no pharmacological agents listed in the treatment protocols for OSA, and medication use is restricted to the prevention and correction of precipitating conditions such as obesity and hypothyroidism [35, 36]. There is growing evidence that SGLT-2 inhibitors may reduce OSA severity [16, 17, 37, 38]. SGLT2 inhibitors may benefit patients with OSA by promoting weight loss. OSA severity can be improved by reducing weight and reducing diet alone. This effect is facilitated by SGLT2 inhibitors by increasing lipolysis and decreasing central obesity [38, 39]. As fat deposits around the neck and thorax may worsen upper airway collapsibility, weight loss may have a beneficial effect on airway collapse and AHI. However, the meta-analysis by Mir et al. included 65 patients with OSA and T2DM, and showed that AHI, BMI, and systolic blood pressure (SBP) all decreased and SpO_2_ increased with SGLT2 inhibition, though these results were not statistically significant [40].

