## Trial status

At the time of manuscript submission, the enrollment of volunteers is ongoing. The study has been ongoing from October 2021. The protocol version is 2.0 (issue date 5 July 2021).

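### Exclusion 11 bars earlier dapagliflozin only, so a current or recent user of another SGLT2 inhibitor can enter and carry a class effect into the baseline AHI

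*Protocol article*

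**What the plan says.** All references are to the protocol article.

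- **Eligible participants, Table 1.** A patient must satisfy every inclusion criterion and no exclusion. Exclusion 11 is "Previous use of dapagliflozin". No other item names an SGLT2 inhibitor. Exclusion 10 removes patients with HbA1c of 7.0% or more.
- **Study design, text under Fig. 1.** "During the research process, the participants cannot take other types of SGLT2 inhibitors such as empagliflozin and canagliflozin". The background regimen described there (beta-blocker, ACE inhibitor or ARB, MR antagonist) contains no SGLT2 inhibitor, and dapagliflozin begins one day after the baseline sleep recording.
- **Study design.** "Following the inclusion and exclusion criteria, a pre-therapeutic evaluation will be conducted", and this evaluation includes the polygraphy.
- **Follow-up and duration of the study, Table 2.** Visit 1 falls on days -7 to 0 under "Screening and randomization". AHI is measured at visit 1 and at visit 4 (day 84). Medical history is taken at visit 1, and "Combined medication" is recorded at every visit.
- **Sample size.** The effect is 8 events/h with SD 6, "assuming that AHI would not change in the control group".
- **Discussion.** "There is growing evidence that SGLT-2 inhibitors may reduce OSA severity". The same section also cites a meta-analysis in 65 patients whose improvements were not statistically significant.
- **Trial status.** At submission, "the enrollment of volunteers is ongoing".

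**The concern.** The entry rule is narrower than the in-trial rule. Someone who took dapagliflozin at any time is barred, yet someone who took empagliflozin last week is not, and the article gives no reason for the difference. The in-trial ban shows that the authors regard sister drugs as able to disturb the comparison.

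The outcome is a change score, so whatever lowers AHI at visit 1 enters it directly. If the ban does not reach visit 1, a current user's baseline is recorded on the class. If it does, the user has to stop at entry and the baseline may be recorded soon afterwards. Either way, a treated user starts with part of the expected gain already in place, and a control user may rise as the effect wears off, against the planning assumption of no change in that arm. At stake are power and, in some cases, the size of the estimated effect.

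**Working it through.** **1. The plan's own figure.** Inputs from Sample size: difference 8, SD 6, power 90%, alpha 5% (taken as two-sided), 20% loss; 1:1 allocation from Randomization process. The normal formula gives

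n per arm = 2 × (1.960 + 1.282)² × 6² / 8² = 11.8, rounded up to 12.

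The total is 24, and 24 / 0.80 = 30, which is the stated number. With 12 completers per arm, a two-sided t test has power 87.7%; this is the reference value below.

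**2. Does any other entry rule close the gap?** No. The HbA1c rule leaves in a user with HbA1c below 7.0%. Exclusion 1 concerns other studies. The in-trial ban says nothing about use before entry.

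**3. What a user does to the endpoint.** The documents give no user share, carry-over or reversal, so these are assumptions:

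- f = share of patients who are users: 5% or 10%, i.e. 1.2 or 2.4 of 24 completers.
- c = share of an 8-event class effect still present at visit 1. c = 1 means on drug, c = 0.5 means recently stopped, c = 0 means gone.
- r = share of that remainder which controls lose by day 84.

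The 8-event class effect is borrowed from the planning difference. For AHI change:

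- Dapagliflozin arm: mean -8(1 - cf), variance 36 + (8c)² f(1 - f).
- Control arm: mean 8crf, variance 36 + (8cr)² f(1 - f).
- Difference: -8 + 8cf(1 - r).

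Worked example, c = 1, r = 0, f = 0.10: the treated mean is -8 × 0.9 = -7.2 and the control mean is 0, so the difference is -7.2. The treated variance is 36 + 64 × 0.09 = 41.76 and the control variance 36, so the pooled SD is √38.88 = 6.24. The noncentrality is 7.2 / (6.24 × √(2/12)) = 2.83, and power is 77.1%.

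| Visit 1 state | Reversal in controls | Difference, f = 5% / 10% | Power, f = 5% / 10% |
|---|---|---|---|
| No users, or effect gone | – | -8.0 | 87.7% |
| On drug (c = 1) | full (r = 1) | -8.0 / -8.0 | 85.0% / 82.6% |
| On drug | half (r = 0.5) | -7.8 / -7.6 | 84.3% / 80.7% |
| On drug | none (r = 0) | -7.6 / -7.2 | 82.7% / 77.1% |
| Recently stopped (c = 0.5) | full | -8.0 / -8.0 | 87.0% / 86.4% |
| Recently stopped | half | -7.9 / -7.8 | 86.5% / 85.2% |
| Recently stopped | none | -7.8 / -7.6 | 85.7% / 83.5% |

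A simulation of the mixture, 100,000 trials per cell, agreed within 0.005.

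**4. Direction.** With a shared class effect, users can only weaken the contrast or add noise. With full reversal the difference stays at -8 and only the variance grows.

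**5. Dropping users.** Removing two patients, one per arm, leaves 11 per arm and power 84.5%.

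**The case against.** The wording gap is not in dispute; its importance is.

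- **The ban may already cover visit 1.** Table 2 counts screening as part of the research phase, so the on-drug rows may not arise. This is a fair reading. It leaves the recently-stopped rows, where the loss is at most about 4 percentage points.
- **77% is a corner case.** It needs 10% users, the full effect at visit 1 and no loss of it in controls over 12 weeks during which sister drugs are banned. This stands, and the figure should be read only as an outer bound.
- **Few users are likely.** Background therapy lists no SGLT2 inhibitor, HbA1c of 7.0% or more is excluded, and the Background section presents dapagliflozin as the agent labelled domestically for HFrEF, so earlier class use for heart failure may often have been dapagliflozin itself. This stands as a reason for low priority. A patient with well-controlled diabetes on empagliflozin remains eligible.
- **A washout would fit the mechanism better than a lifetime bar.** It would also work. But the protocol already applies an any-previous-use rule to dapagliflozin, and extending that rule needs no new window to justify.
- **The article is condensed, and washout detail may sit in the full protocol.** That may be true of a washout. It does not explain exclusion 11, which is printed in full and limited to one drug.

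**Conclusion.** The point holds as a minor one. Exclusion 11 is drawn more narrowly than the protocol's own in-trial rule, and current or recent users of a sister drug meet Table 1 as written. Across the scenarios above, power is 77% to 87%, against 88% without users or with no effect left at visit 1; on the reading that the ban covers visit 1, with half the effect remaining, it is 83.5% to 87.0%.

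These figures depend on assumed values for the user share, an 8-event class effect, the carry-over and the reversal. The protocol supplies only the expected direction of the class effect, not its size for the sister drugs. Randomisation spreads users evenly in expectation, so the harm is lost precision or dilution, and it does not produce a false positive. With about 24 completers, one or two such patients are enough to matter slightly.

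**What to change.** Reword exclusion 11 to *current or previous use of any SGLT2 inhibitor*. This brings entry into line with the in-trial ban and leaves the sample size at 30.

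Because enrolment had begun, identify users among patients already randomised from the visit 1 history and medication record, and report the primary outcome without them in both arms as a supportive sensitivity analysis. Use before randomisation is a baseline characteristic, so this removal keeps the comparison randomised.

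The cost is one phrase by amendment; the visit 1 records are already part of the schedule. A few patients become ineligible, including some whose use ended long ago and would have done no harm. The sensitivity analysis will say little if only one or two patients are removed. With half the effect left at visit 1, removing two users (84.5%) gives less power than keeping them in two of the three reversal cases (86.4% and 85.2%, against 83.5% in the third), so it should remain supportive.

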### Follow-up and duration of the study

There will be two visits at the clinical research center, one before (baseline) and one after (3 months follow-up) the dapagliflozin intervention. Data collection to assess efficacy of the intervention will be managed by research team members. An overview of the measures used at each of the four time points is illustrated in Table 2. For improving the compliableness of patients, the strategies are as follows: (1) adhere to the principle of voluntary participation and explain the benefits of this study to the participants and the importance of treatment and adherence to the treatment. Health education process could increase the related knowledge, change the behavior, and enhance the compliance of patient. (2) Written informed consent will be obtained from each patient before they begin the trial. All participants will fill in informed consents. (3) The treatment is free for participants, such as the relevant examination expenses and the telephone bill, traffic expenditures, and analgesic drugs incurred during the treatment and follow-up. (4) Record participants’ contact methods in detail, including mobile phone, WeChat, and e-mail for contact and follow-up.

**Table 2 Tab2:** Administration of study measures by assessment period

Research phase	Screening and randomization	Treatment period		
Interview	1	2	3	4
Research date	− 7–0	28 ± 2	56 ± 4	84 ± 6
Baseline information				
Informed consent	●			
General information	●			
History	●			
Physical examination	●	●	●	●
Treatment				
Inclusion/exclusion criteria	●			
Combined medication	●	●	●	●
Compliance		●	●	●
Completion of research				●
Inclusion/exclusion criteria				
PSG	●			
Echocardiography	●			
Security index				
Blood routine	●			●
Urine routine	●			●
Blood biochemical	●			●
Electrocardiogram	●			●
Adverse event assessment		●	●	●
Outcome				
AHI	●			●
Epworth Somnolence Scale (ESS)	●	●	●	●
Echocardiography	●			●
NT-proBNP	●			●
Quality of life as measured by the Minnesota Living with Heart Failure Questionnaire	●	●	●	●
EQ—5D—3L				
L_SpO2_	●			●
Inflammatory factors	●			●

### Sample size

The sample size calculation for this trial was performed using the PASS 11.0 program [25]. The primary end point of the main study was the decreasing value of Apnoea–Hypopnoea Index (△AHI). Based on existing data, a 8 ± 6 events/h change in AHI events/h between the control and therapy groups was considered clinically relevant (assuming that AHI would not change in the control group) [26–28]. Based on a power of 90% and an alpha value of 5%, it was calculated that a sample size of 30 patients (considering the 20% sample loss rate) would be sufficient to detect a difference in the effect size of at least 10%. Data monitors from the two centers will supervise the study process at a fixed period.

### Randomization process

As the sample size of the study was not large, we adopted a simple random method. Participants will be assigned a randomization code according to their sequential numbers and randomly allocated into one of two groups with a 1:1 ratio in the operating room.

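### A small sample is given as the reason for simple randomisation; it is a reason against it, and with 30 patients at two centres chance imbalance between arms is likely

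*Protocol article*

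**What the plan says.** The Randomization process section gives both the method and its reason: "As the sample size of the study was not large, we adopted a simple random method". Patients are then "randomly allocated into one of two groups with a 1:1 ratio in the operating room". No blocking, stratification factor or minimisation is mentioned. That allocation is unrestricted is inferred from the word simple and from this absence; the article does not say unstratified.

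The Study design section says "The study will be conducted in two research centers". The Sample size section arrives at 30 patients after allowing for 20% loss, from "a 8 ± 6 events/h change in AHI events/h between the control and therapy groups", 90% power and 5% alpha. The Statistical methods section names a t test for measurement data and no centre or baseline term. The Discussion concedes that the trial has neither double blinding nor placebo.

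**The concern.** Simple randomisation relies on the number of patients to even things out. In a large trial the relative difference between arms becomes negligible; in a trial of 30 it often does not. A small sample is therefore an argument for restricting the randomisation, and the article uses it as an argument for leaving it unrestricted.

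Two things are at stake. Unequal arm sizes lower power somewhat. More important, the arms may differ by chance in centre mix and in prognosis, baseline AHI above all, with few patients to absorb the difference and no adjustment in the analysis that the article names.

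**Working it through.** **Inputs.** Difference 8 events/h and SD 6 events/h, power 90%, alpha 5%, loss 20% (Sample size); ratio 1:1 (Randomization process); two centres (Study design). Assumed because not stated: a two-sided test, centre sizes, and loss that does not depend on arm.

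**1. The plan's own figure.** Two-sided normal approximation, per arm:

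n = 2 × (1.960 + 1.282)² × 6² / 8² = 11.8, rounded up to 12.

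Total 24, and 24 / (1 − 0.20) = 30. The stated 30 is reproduced as a total for both arms. A one-sided calculation would give 25, and an exact two-sided t calculation 33.

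**2. Arm sizes under simple 1:1 randomisation.** The number in one arm is Binomial(N, 0.5); the probability of a split k:(N − k) or worse, with k > N/2, is 2 × P(X ≥ k).

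| Split or worse | Probability |
|---|---|
| 18:12 of 30 | 36% |
| 19:11 of 30 | 20% |
| 20:10 of 30 | 9.9% |
| 21:9 of 30 | 4.3% |
| 15:9 of 24 | 31% |
| 16:8 of 24 | 15% |
| 17:7 of 24 | 6.4% |

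An exact 15:15 split has probability 14%.

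**3. Centre mix.** Let centres have a and b patients (a + b = 30), with X ~ Binomial(a, 0.5) and Y ~ Binomial(b, 0.5) allocated to one arm. The difference between the arms in the share from the first centre is D = |X/(X + Y) − (a − X)/(30 − X − Y)|. Exact enumeration gives:

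| Centre sizes (assumed) | P(D ≥ 20 points) | P(D ≥ 30 points) |
|---|---|---|
| 15 and 15 | 36% | 11% |
| 20 and 10 | 26% | 10% |

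**4. Power at unequal arms.** Two-sided t test, n₁ + n₂ − 2 degrees of freedom, noncentrality 8 / (6 × √(1/n₁ + 1/n₂)). For 12:12 this is 8 / (6 × 0.408) = 3.27; for 16:8 it is 8 / (6 × 0.433) = 3.08.

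| Analysed | Split | Power |
|---|---|---|
| 30 | 15:15 | 94.1% |
| 30 | 20:10 | 91.4% |
| 30 | averaged over all splits | 93.3% |
| 24 | 12:12 | 87.7% |
| 24 | 16:8 | 83.7% |
| 24 | averaged over all splits | 86.2% |

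The average loss is 94.1 − 93.3 = 0.8 point with 30 analysed and 87.7 − 86.2 = 1.5 points with 24.

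**5. With restriction.** Take permuted blocks of 4 within centre as an illustration. The imbalance is at most 2 in each centre, so the overall split is never worse than 17:13, where power with 30 analysed is 93.7%. With centres of 15 and 15, each splits 8:7, and the arms' centre shares differ by at most 8/15 − 7/15, about 7 points.

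**The case against.** Simple randomisation is a legitimate method. The comparison is unbiased, and over repeated randomisations the t test allows for chance imbalance. A reader might infer that treatment is confounded with centre; the documents do not support that. Only chance imbalance in a single realised allocation is possible, and nothing shows that the centres differ systematically. The primary outcome is a within-patient change in AHI, so a stable centre difference in recording or scoring largely cancels. The article also fixes one scoring standard and requires guideline-based therapy at both sites. This stands, and it limits the centre argument to differences in change. It does not deal with baseline AHI: change usually depends on the starting value, particularly when patients enter above a threshold.

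A reader might also infer a serious loss of power. The averages do not bear this out. At 20:10 with all 30 analysed, power still exceeds 90%, and the shortfall to 87.7% with 24 completers is already there at 12:12, so the randomisation does not cause it.

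The 1:1 ratio is not contradicted either. Under simple randomisation it is an allocation probability and not a promised count.

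Finally, the reference to an operating room might suggest that the described procedure was not the one carried out. The article has other slips of wording, such as a misspelt drug name in the group description, and a wrong location does not show that sequential coding and 1:1 allocation were not followed.

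A centre term may sit in an analysis plan that is not shown. Custody of the list and timing of release are details that an article may leave to the full protocol, and no fault is found in their absence. None of this rescues the stated rationale, which is on the page and wrong.

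**Conclusion.** The concern holds in a limited form. The article's reason for simple randomisation is inverted, and at this size the consequence is not rare: one trial in five would split 19:11 or worse, and between about a quarter and a third would have arms whose centre shares differ by 20 points or more. The latter range rests on the assumed centre sizes, and all the figures rest on 30 being the total, which the article's own inputs support.

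The effect on power is minor on average, although a 16:8 split of completers would cost 87.7 − 83.7 = 4.0 points. The larger cost is a less precise and less readily interpreted comparison when centre or baseline severity happens to differ between arms, since the analysis as named has no term for either. This is an improvement that should be made; it is not a flaw that invalidates the trial. The operating room wording is a separate editorial correction.

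**What to change.** - **Randomisation.** For patients not yet randomised, use permuted blocks of randomly varying size, stratified by centre. Those already randomised keep their allocation; the ratio is 1:1 in both phases, so they can be analysed together.
- **Rationale.** Delete the sentence that justifies simple randomisation by the small sample.
- **Analysis.** Put centre and baseline AHI in the primary model, and fix this before any comparison of outcomes by arm, including the planned interim analysis. Stratifying by centre does not balance baseline AHI, so the model term is needed in either case.
- **Text.** Replace the operating room with the actual place or means of allocation.

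The Trial status section says that enrolment has been under way since October 2021, so few patients may remain. In that case the model adjustment alone gives most of the benefit.

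The cost is a new allocation list and a protocol amendment through the ethics committees. The sample size stays at 30. Two covariates reduce the residual degrees of freedom with 24 completers from 22 to 20. Blocks are slightly more predictable than simple randomisation when treatment is not blinded; randomly varying block sizes limit this.
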